### Sample size estimation

Primary outcome of this trial is stroke survivors’ self-efficacy in performing self-management behaviours measured by the Stroke Self-Efficacy Questionnaire at eight weeks after randomisation. A sample size of 64 per group (128 for two groups) is required to detect a significant mean difference in self-efficacy between groups for a medium effect size of 0.5 [14] with significance set at 0.05 and a power of 0.8 [15]. Taking into consideration an attrition rate of 19 % over six months among stroke survivors [14], the final sample size is 160 (80 participants per group). Recruitment of participants is anticipated to take 12 months.

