### Statistical analysis

Statistical analyses will be performed using the IBM SPSS Statistics version 22 (SPSS Inc., Chicago, IL, USA). All primary analyses will be conducted on an intention-to-treat basis. No interim analyses will be undertaken. Descriptive statistics will be used to summarise participants’ baseline characteristics and outcome variables. All continuous outcomes will be assessed for normality in distribution. Appropriate transformation of skewed data will be performed before analysis. Chi-square tests and independent t-tests will be used to compare the demographic and clinical characteristics, and mean scores of outcomes between the intervention and control groups at baseline. A generalised estimating equation (GEE) model will be employed to assess differential change of the primary and secondary outcomes across the time points (baseline and eight weeks after randomisation) between the two groups. Adjustment will be made for potential confounding demographic and clinical variables, including gender, age, number of strokes, NIHSS, and the Barthel ADL Index, that were ‘unbalanced’ between the two groups (*p* < 0.25) [31, 32]. The longitudinal association of self-efficacy and outcome expectation with secondary outcomes will be examined using GEE model. GEE model can account for intra-correlated repeated measures data and accommodate missing data caused by dropouts, provided the data are missing at random [33], and is particularly suitable for intention-to-treat analysis without imputation for missing data. Significance level will be set at two-sided *p* < 0.05 and all statistical tests will be two-tailed.

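### The plan justifies no imputation by saying GEE is valid under missing at random; unweighted GEE in general is not, so dropout tied to baseline SSEQ differently by arm can bias the effect

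*Protocol article*

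**What the plan says.** All references are to the protocol article.

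- **Model.** Statistical analysis: "A generalised estimating equation (GEE) model will be employed to assess differential change of the primary and secondary outcomes across the time points", the two points being baseline and eight weeks after randomisation. Baseline SSEQ is therefore one of the two responses.
- **Missing data.** The same section says GEE can "accommodate missing data caused by dropouts, provided the data are missing at random" and that it "is particularly suitable for intention-to-treat analysis without imputation for missing data". No weighting is mentioned.
- **Covariates.** Gender, age, number of strokes, NIHSS and the Barthel index are named as candidates. A variable is added only if the arms differ on it at p < 0.25, not because it predicts dropout.
- **Attrition.** Sample size estimation: "Taking into consideration an attrition rate of 19 % over six months among stroke survivors". The outcome assessment is at 8 weeks.

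**The concern.** The condition that the plan calls sufficient is not sufficient for the method it names. Dropout that depends on an observed baseline SSEQ score is missing at random. Unweighted GEE is consistent in general only if missingness is completely at random or depends on nothing beyond the covariates in the mean model. Baseline SSEQ is not such a covariate, and the p < 0.25 rule does not make it one.

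At stake is the primary treatment effect. If less confident people leave one arm more than the other, the week-8 means come from differently selected groups, and nothing in the stated analysis is certain to correct that. The effect estimate shifts and the type I error can exceed 5%. Differential dropout is possible because participants know their allocation (Blinding section).

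**Working it through.** **1. The plan's own figure.** The inputs are "for a medium effect size of 0.5" and "with significance set at 0.05 and a power of 0.8"; the test is two-sided ("Significance level will be set at two-sided"). The exact t-test power is 0.795 at 63 per group and 0.801 at 64, so 64 is right. Allowing for attrition, 64 / (1 − 0.19) = 79.01, rounded up to 80 per group, 160 in all. The sample size reproduces and is not in dispute.

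**2. What GEE estimates.** Take saturated group-by-time means and a working correlation α. With baseline complete, the estimating equations give, within each arm:

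week-8 mean = completers' week-8 mean − α × (completers' baseline mean − all-randomised baseline mean)

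Let β be the regression slope of week 8 on baseline, in baseline-SD units: β = ρ × (SD at week 8 / SD at baseline). Let m be the mean baseline z-score among those retained in an arm. Then

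**bias in the group-by-time effect = (β − α) × (m in intervention − m in control).**

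Working independence sets α = 0, so with equal SDs the bias is ρ × (difference in m).

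**3. Assumptions not in the documents.** ρ is 0.5 or 0.7. Dropout is logistic in baseline score, with a log-odds slope of 1 per SD (odds ratio about 2.7). SDs are equal unless stated. For dropout rates below 19%, a constant hazard gives 1 − 0.81^(8/26) = 6.3% at 8 weeks; 10% is shown as well because the hazard may be higher early.

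**4. Results under working independence.** In the one-arm case m is 0 in the other arm; in the opposite case m has opposite signs, so its difference doubles. Type I error is from simulation with 80 per arm and true effect 0, as the range over ρ 0.5 to 0.7 and repeated runs.

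| Dropout | m | One arm: bias (SD), ρ 0.5 / 0.7 | Type I | Opposite: bias (SD), ρ 0.5 / 0.7 | Type I |
|---|---|---|---|---|---|
| 6.3% | 0.059 | 0.03 / 0.04 | 5–6% | 0.06 / 0.08 | 7–10% |
| 10% | 0.091 | 0.05 / 0.06 | 6–8% | 0.09 / 0.13 | 8–15% |
| 19% | 0.165 | 0.08 / 0.12 | 8–13% | 0.16 / 0.23 | 15–34% |

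Example: at 19%, ρ 0.7, opposite directions, 0.7 × (0.165 + 0.165) = 0.231 SD, which is 0.231 / 0.5 = 46% of the design effect. At 6.3%, ρ 0.5, one arm, 0.5 × 0.059 = 0.03 SD, or 6%.

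**5. When it cancels, and when it does not.**

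- Same slope and same rate in both arms: the difference in m is 0 and so is the bias. Simulation agrees.
- Same slope, but 28% dropout in intervention and 10% in control: m is 0.237 and 0.091, so at ρ 0.5 the bias is 0.5 × 0.146 = 0.07 SD.

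**6. Exchangeable structure.** The working correlation is now estimated.

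- Equal SDs, ρ 0.5, opposite selection at 19%: the estimated α is 0.463, so the bias is (0.5 − 0.463) × 0.33 = 0.012 SD. Across scenarios the simulated residual is about 0.02 SD or less.
- Week-8 SD 1.3 times baseline, ρ 0.7: β = 0.91 and the estimated α is 0.650, so the bias is (0.91 − 0.650) × 0.33 = 0.086 SD (simulated 0.087). Under independence the same case gives 0.91 × 0.33 = 0.30 SD.

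**7. Comparator.** An analysis that conditions on the baseline score had bias of about 0 throughout, on the same simulated data.

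**The case against.** The strongest reply is that this is a narrow wording error with little practical effect. Four parts of it deserve an answer.

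- **A sensible working correlation nearly removes the bias.** This is true for two time points and a continuous outcome when SDs are similar. The article names no structure, which a condensed article may leave to a fuller document, so that silence is not itself a fault. But the stated sentence makes validity depend on missing at random alone, not on the working covariance. The protection is neither claimed nor secured.
- **19% is the wrong exposure.** This stands. It is a six-month rate used to inflate the sample, and outcomes are taken at 8 weeks. The lower rows of the table may be nearer the mark.
- **Bias needs selection or dropout rates that differ by arm.** This also stands. A reader might infer that the extra programme contacts will drive such dropout. The documents do not support that: missing a session is not missing the outcome, both arms are assessed face to face at home, and eligibility requires being able to attend. Lack of blinding keeps it possible, no more.
- **The largest figures are extreme.** A reader might take 34% type I error as the expected consequence. It needs less confident people to leave one arm while more confident people leave the other, at the six-month rate and under working independence. Nothing in the documents points to that pattern.

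Nor do the documents support the inference that GEE is always biased under missing at random, or that this trial's primary result must be wrong.

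**Conclusion.** The point holds in limited form. The stated validity condition is wrong as a general property of unweighted GEE, and it is the plan's reason for having no imputation. An unseen analysis plan could choose a better analysis but could not make that sentence correct.

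The consequence is conditional. It requires dropout that depends on baseline SSEQ, with a pattern or rate that differs by arm, and a working structure that does not capture the within-person dependence. When all three hold, the bias ranges from a few hundredths of an SD at 8-week-type attrition with selection in one arm to about a fifth of an SD in the adverse case at 19%. Its direction depends on who leaves which arm. These sizes rest on the assumed correlation, slope and SD ratio, for which the documents give no values. It merits correction because the remedy costs so little, not because serious bias has been shown.

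**What to change.** 1. Correct the sentence: unweighted GEE in general needs data missing completely at random, or missingness that depends only on covariates in the mean model.
2. Make the primary analysis one that is valid under missing at random. Examples are a REML mixed model with unstructured covariance over the two time points, or week-8 ANCOVA on baseline score, both in the package already named. ANCOVA on completers is valid here if dropout depends on baseline score and arm and the regression is correctly specified.
3. If GEE is kept, specify a non-independence working correlation. In addition, either apply multiple imputation that includes baseline score and arm, or report a baseline-adjusted sensitivity analysis.

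The cost is a little more analysis work. The sample of 160 is unaffected, and no new data or participants are needed. None of these options protects against dropout that depends on the unobserved week-8 score.

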## Discussion

To the best of the authors’ knowledge, this is the first randomised controlled trial which examines the effectiveness of a nurse-led stroke self-management programme on recovery among Chinese community-residing stroke survivors. This study adopts Bandura’s constructs of self-efficacy and outcome expectation [16] which considers both efficacy and outcome expectancy beliefs and the methods for improving these, as the underlying theoretical premise to guide the programme design, implementation and evaluation. Maintaining hopes for positive outcomes would be important incentives to stroke survivors’ pursuance in stroke self-management behaviours given a certain level of physical functioning [4]. It is expected that stroke survivors receiving the stroke self-management programme will have improved self-efficacy, outcome expectation, and performance of self-management behaviours. Enhanced health-related quality of life and level of community reintegration, and decreased depressive symptoms are also be expected. The study results will provide valuable evidence to inform future identification and evaluation of best approaches to deliver stroke self-management programmes to enhance community-residing stroke survivors’ recovery.

## Abbreviations

ADL: Activities of Daily Living
GEE: Generalised Estimating Equation
MMSE: Mini Mental State Examination
NIHSS: National Institutes of Health Stroke Scale
SSEQ: Stroke Self-Efficacy Questionnaire
SSQOL: Stroke Specific Quality of Life Scale
